## Analysis of Outcome Measures

Descriptive statistics (mean, standard deviation, standard error, range, etc) will be calculated for each outcome for each group. Differences in the primary and secondary outcomes will be compared between intervention and control groups.

Mean changes in blood pressures and cardiovascular fitness will be compared across the population and correlated with cardiovascular endpoints including cardiac structure and function reported from cardiac MRI and echocardiogram.

Demographic and physiological characteristics of the participants will be added to regression models as covariates to explore the determinants of change in blood pressure comparing preterm and full term born participants.

Statistical analysis will be carried out using a computer software package, applying statistical methods to analyse dependent and independent variables within the study database. The variable will be plotted to categorize distribution and assess if the data is normally distributed which will guide the statistical methods. Methods such as the Student T-test will assess for differences between the groups and linear regression analysis will be used to assess if the study variables can explain differences in primary outcome. It is hoped that this will then allow for clear understanding on how the cardiovascular system adapts following exercise training and how remodelling may differ according to birth history and early life exposures. For the sub-study, the statistical analysis will be carried out using a computer software package and data will be analysed using paired and independent t-test. This will access the variability of circulating blood biomarkers within the same participant across both visits and also between each participant.

A detailed statistical analysis plan will be written with our statistical team and will be completed before receipt of the data.

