| To investigate hepatic remodelling and mean change in hepatic adiposity pre and post exercise intervention compared to control | Liver MRI (MRI sub-group n=100)  Liver MRI Endpoints   - Structure and volume - Intra-hepatic lipid content - Steatohepatitis - Hepatic fibrosis | Measured at:  - baseline  - upon completion of 16 week intervention |
| To investigate the correlation between physical activity behaviour change and participants’ cognitive and psycho-social determinants of exercise including self-efficacy to exercise, motivations to exercise. | Objective measure of physical activity (7 day wear of activity monitor)  Self-reported questionnaire responses, including self-reported physical activity questionnaires, cognitive and psycho-social questionnaire items and self-efficacy measures. | Measured at:  - baseline  - upon completion of 16 week intervention  - 52 weeks post randomisation |
| **Tertiary Objectives** |  |  |
| Participant experience: assessment of individual experience following intervention | Structured interview (participants) | End of trial period |
| Economic evaluation: assessment of feasibility for scaling intervention to multi-centre trial including intervention process evaluation | EQ-5D-5L health questionnaire results  Structured interviews (study team and personnel)  Review of medical notes/GP consultations | End of trial period |

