**Self-monitored physical activity and support for sustained behaviour change**

During the 16 week supervised exercise intervention training instructors and intervention staff will support global increase in self-monitored physical activity. Instructors will support the three most effective behaviour change strategies to promote increased physical activity, including participant self-monitoring, goal setting and regular feedback^50,51^. Participants will be provided with accelerometer-based activity monitors, equivalent to the Fitbit or similar device, to allow self-monitoring and target increased physical activity outside of supervised sessions.

The daily physical activity target will be based on the recommended guideline of daily step counts of 10,000 steps per day. Increasing steps counts will be facilitated by titrating a proportional increase from baseline activity to achieve the minimum target of 10,000 steps.

Participants will be consented to allow investigators access to the data collected from wear of the Fitbit or similar device. The information will be used to facilitate feedback on physical activity, goal setting and maintenance of physical activity behaviours.

Following the supervised intervention participants will be encouraged to continue to use their activity monitor and maintain physical activity goals. Remote support will be provided to facilitate feedback and maintenance of physical activity. The intervention team will review continued use of the activity monitor and activity targets at a minimum of 2 weeks. If physical activity is declining or wear time has declined participants with be contacted and offered support to re-engage with behavioural targets. Contact will be maintained via email, text messaging and phone calls. If required, participants will be offered face-to-face support, communication will incorporate motivational strategies to maintain activity goals.

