## The Number of Participants

***Primary Outcome 24-hour awake ambulatory blood pressure***

Our systematic review and meta-analysis of randomised control trials identified an average decrease of 5.4mmHg in systolic blood pressure (SBP) post-intervention via supervised exercise in young adults with prehypertension (mean systolic blood pressure at baseline 126 mmHg). The post intervention standard deviation of change was 8.7 mmHg. Our available cross-sectional pilot data suggests that change will be higher in the preterm born participants and participants exposed to maternal hypertension during pregnancy. To calculate the sample size we have been conservative and used an estimated change of 5 mmHg following 4 months of intervention. We have used a SD of 11.3 from the pooled SD for ambulatory systolic blood pressure from our cross-sectional pilot data. To observe a treatment effect on systolic blood pressure of 5mmHg, powered to 80% (p=0.05) requires a total sample size of 164 participants. The SD deviation for the pooled 24 hour awake diastolic blood pressure is 8.3 mmHg. To observe a treatment effect on diastolic blood pressure of 5mmHg, powered to 80% (p=0.05) requires a total sample size of 114 participants. The power calculations for systolic blood pressure are used to determine the final sample size, with adjustment to 200 participants to allow for 18% attrition. To ensure primary objectives for the study are answered the study team may recruit additional participants to replace those who drop out of the study.

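### Section 11.3 relates changes in fitness and blood pressure to cardiac endpoints over the whole study population without a term for allocation, so an exercise effect on both measures could reappear as a mechanistic correlation

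*Supplement*

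**What the plan says.** Protocol section 11.3 (Analysis of Outcome Measures) first says that primary and secondary outcomes will be compared between intervention and control. In a separate paragraph it adds: "Mean changes in blood pressures and cardiovascular fitness will be compared across the population and correlated with cardiovascular endpoints", and names cardiac MRI and echocardiography as sources of those endpoints. It states no allocation term, within-arm analysis, test or significance level for these correlations.

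The next paragraph does name covariates, for a neighbouring regression: "Demographic and physiological characteristics of the participants will be added to regression models as covariates to explore the determinants of change in blood pressure". Allocation is not among them. The section goes on to hope that the analyses will clarify how the cardiovascular system adapts to training, and it ends: "A detailed statistical analysis plan will be written with our statistical team and will be completed before receipt of the data". That plan is not among the documents shown.

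A related secondary objective in section 5 reads "To investigate the correlation between physical activity behaviour change" and pairs that change with psycho-social determinants of exercise such as self-efficacy and motivation. Section 9 says of the intervention: "Instructors will support the three most effective behaviour change strategies to promote increased physical activity".

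**The concern.** The trial is designed to raise fitness in one arm, and the MRI sub-study is sized to detect cardiac change between groups. If both happen, the exercise arm sits higher on both axes of a pooled scatter plot. The gap between the two clouds alone gives a non-zero correlation, even if participants within an arm who gained more fitness show no more cardiac change.

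The randomised effect on each measure is already estimated in the between-arm comparison. Reading the pooled correlation as a link between fitness gain and remodelling would count that effect a second time, as evidence of mechanism. The same could happen with activity change and self-efficacy if post-baseline values of both are used, since the intervention may act on both.

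**Working it through.** **Planning figures reproduced first.** Section 11.2 states: "To observe a treatment effect on systolic blood pressure of 5mmHg, powered to 80% (p=0.05) requires a total sample size of 164 participants". With SD 11.3, the normal formula gives 2 × (1.96 + 0.84)² × (11.3/5)², about 80.2, so 81 per arm. The t-test version gives 82 per arm, 164 in total, as stated. Then 164/0.82 = 200, which matches the 18% attrition allowance. For LVM index, 10% of 66.5 is 6.65. With SD 10.9 and 50 per group the t-test power is 85.6%, against 85% stated.

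**Cardiac shift (assumption).** The effects the MRI sub-study is sized to detect are:
- LVM index: 6.65/10.9 = 0.61 SD
- End-diastolic volume: 7% of 72.2 = 5.05; 5.05/9.3 = 0.54 SD

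These are detectable differences, not predictions. Section 11.2 gives no effect size for echocardiography, so the same values are borrowed for it.

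**Fitness shift.** From eTable 4 at 16 weeks, the SD is the interval width divided by 3.92 and then by √(1/n₁ + 1/n₂):
- 3.0 (1.5 to 4.5), 45 v 92: 0.765/0.182 = 4.2; 3.0/4.2 = 0.71 SD
- 2.4 (0.8 to 3.9), 39 v 92: 0.791/0.191 = 4.1; the interval midpoint 2.35/4.14 = 0.57 SD

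**Pooled correlation with no within-arm association.** With 1:1 allocation, unit SD within arms and arm differences d₁ and d₂:

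r = (d₁d₂/4) / √[(1 + d₁²/4)(1 + d₂²/4)]

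Example: d₁ = 0.64, d₂ = 0.61 gives 0.0976/√(1.1024 × 1.0930) = 0.089.

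**Rejection rate at two-sided 5%** (assumed; no level is stated). With z = atanh(r) × √(n − 3), the rate is Φ(z − 1.96) + Φ(−z − 1.96). Applying 18% attrition leaves 82 of 100 MRI pairs and 164 of 200 echo pairs.

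| Fitness shift (SD) | Cardiac shift (SD) | r | n = 82 | n = 164 |
|---|---|---|---|---|
| 0.57 | 0.54 | 0.071 | 9.8% | 14.9% |
| 0.64 | 0.61 | 0.089 | 12.4% | 20.5% |
| 0.71 | 0.61 | 0.098 | 14.0% | 23.7% |
| 0.57 | 0.20 | 0.027 | 5.7% | 6.4% |
| 0.71 | 0.30 | 0.050 | 7.3% | 9.7% |
| 0.71 | 0 | 0 | 5% | 5% |

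Simulation agrees with these figures. When each arm is centred on its own mean, the simulated rate is 4.8 to 5.3% in every case.

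**Sensitivity to the fitness SD.** The 4.1 to 4.2 comes from an adjusted model; the SD of raw change is not reported. With an assumed SD of 7, near the cross-sectional values in eTable 4, the shift is 0.34 to 0.43 SD. Against cardiac shifts of 0.54 to 0.61 SD the rate is then about 9 to 12% at n = 164.

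**Blood pressure.** Section 11.2 offers two SDs: "We have used a SD of 11.3 from the pooled SD for ambulatory systolic blood pressure" and "The post intervention standard deviation of change was 8.7 mmHg". The shifts are 5/11.3 = 0.44, 5/8.7 = 0.57 and 5.4/8.7 = 0.62 SD. With the same cardiac shifts the simulated rate at n = 164 is 11 to 19%. The adjusted systolic difference in eTable 2, however, is 0.0 (−2.6 to 2.7). With no shift on one side the rate is about 5%.

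**The case against.** **The statistical analysis plan is not shown and may supply the arm term.** This is the strongest objection. Covariates for an exploratory correlation are commonly settled there, and pooling without adjustment is inferred from the wording rather than stated. What stands is that section 11.3 describes a specific analysis, places it after and apart from the between-arm comparison, lists covariates for the neighbouring regression without allocation, and gives no sign that arm will be included.

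**Section 11.1 mentions a covariate model relating cardiac structure and lifestyle to exercise capacity.** So the topic is not left wholly to a bare correlation. That model does not name allocation either.

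**The cardiac variable is not fixed.** Correlating change in fitness with baseline structure would not create the artefact, because allocation cannot shift a baseline value. This is correct. The point applies to 16-week values or changes, which are what the stated interest in adaptation to training calls for.

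**The pooled correlation is truly non-zero, so rejecting is not an error.** That is fair if the target is the marginal association. It does not serve a mechanistic aim, because the marginal association contains the randomised effect already reported.

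**A reader might infer that a false-positive rate of 10 to 24% is built into the plan.** The documents do not support that. The range needs cardiac shifts as large as the detectable effects, no within-arm association and a 5% test. Its upper part applies MRI effect sizes to echocardiography. The fitness shift comes from a post-hoc split of the exercise arm by volume completed, not from a randomised contrast.

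**A reader might also infer that the self-efficacy objective prescribes the same pooling.** Section 5 does not say so, and the determinants could be baseline values.

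**Conclusion.** The point holds as a conditional weakness in an exploratory analysis. On its natural reading, section 11.3 pools the arms with no allocation term. Where exercise shifts both measures, part of the correlation is the randomised effect in another guise.

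The induced r is small, at most about 0.10, or 1% of variance (0.10² = 0.01). Under the stated assumptions rejection rises to about 10 to 14% for MRI and 15 to 24% for echocardiography. With modest cardiac shifts it is about 5 to 10%. On the reported data the concern applies to fitness and hardly to systolic pressure. The primary ANCOVA and the between-arm comparisons are unaffected.

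**What to change.** In section 11.3, or in the statistical analysis plan if it does not already do so, replace the pooled correlation with a regression of the 16-week cardiac endpoint on its baseline value, allocated arm, the minimisation factors and change in fitness (or pressure). Report the arm-adjusted coefficient and label it a non-randomised association, since participant characteristics can still confound it within arms.

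Use the same arm-adjusted form for activity change against self-efficacy and motivation if post-baseline values or changes enter that analysis.

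The cost is a change of wording and one degree of freedom for the arm term. The reported associations will tend to be smaller.

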# DATA MANAGEMENT

## Access to Data

Direct access will be granted to authorised representatives from the Sponsor or host institution for monitoring and/or audit of the study to ensure compliance with regulations.

## Data Recording and Record Keeping

The study will comply with the Data Protection Regulation (GDPR). The University of Oxford, as sponsor will act as data controller for the study. De-coded study data will be entered onto a password protected, electronic cloud based eCRF provided by Castor EDC. Castor EDC is an electronic data capture and management system that permits secure multi-site access. The server is based in the UK and it complies with relevant law to ensure that the data is held securely. The participants will be identified by a unique study specific participant ID in any database and will not be identifiable from this. Electronic documents that contain participants’ personal identifying information such as the code-break document will be stored on a secure server with restricted access, and Informed consent forms that contain participants’ name will be stored securely in locked cupboards and will be only be accessible to study staff and authorised personnel. The name and any other identifying detail will not be included in any trial data electronic file. Trial data electronic file in excel document format will be transferred to a STATA or SPSS spreadsheet for analysis.

During the study up until publication stage hard copy data will be stored securely and after analysis this will be archived in a secure archive location with restricted access.

Electronic data will be held on secure network drives/hard disks/ servers on password protected computers within locked offices. Backup copies of files will be made regularly weekly and stored on a different secure server/external hard drive. These back up locations will be subject to the same security principles as the primary locations. When datasets are complete, the primary copy will remain at the study site where it will be transferred onto optical media, e.g. DVD/external drives and undergoes archiving for hard copy data. Any copies leaving the study site will be completely anonymised/de-identified.

Personal data (such as contact details and information which could identify a participant) (except from those who have consented for future approach) will be destroyed as soon as it is practical to do so and no later than 12 months after the end of the study. The personal identifiers (name of participant) contained in consent forms and the code break document will be stored or accessed for up to 7 years after study end, after which time the custodian will agree a date for destruction and it will be destroyed confidentially.

As part of our commitment to maximise patient/service user involvement in research, participants will give consent (optional) for their contact details to be retained. This will be kept securely and independently of the study records. This will allow investigators to contact participants about future ethically approved research.

# QUALITY ASSURANCE PROCEDURES

The trial will be conducted in accordance with the current approved protocol, GCP, relevant regulations and standard operating procedures.

Regular monitoring will be performed according to GCP. Data will be evaluated for compliance with the protocol and accuracy in relation to source documents. Following written standard operating procedures, the monitors will verify that the clinical trial is conducted and data are generated, documented and reported in compliance with the protocol, GCP and the applicable regulatory requirements.

A Trial Steering Committee has been formed to oversee the conduct of the trial. The TSC will consist of the [name] (Chief Investigator), [name], [name], and [name], a study statistician, independent statistician, a Professor of Exercise and/or Cardiovascular Prevention from an independent institution and lay committee member.

The TSC will next meet when trial recruitment commences, within 6 months of recruitment opening and after approximately a third of participants have completed their second visit.

A data monitoring committee is being formed. Rates of recruitment, trial compliance, measurement of primary outcome and study attrition will be review annually by the independent members of the Data Monitoring Committee.

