## Procedures for Recording Adverse Events

All AEs occurring during the trial / or until completion of the final study visit that are observed by the Investigator or reported by the participant, will be recorded on the CRF, whether or not attributed to the exercise intervention.

The following information will be recorded: description, date of onset and end date, severity, assessment of relatedness to exercise intervention, other suspect drug or device and action taken. Follow-up information should be provided as necessary.

The severity of events will be assessed on the following scale: 1 = mild, 2 = moderate, 3 = severe.

AEs considered related to the trial treatment as judged by a medically qualified investigator or the Sponsor will be followed either until resolution, or the event is considered stable.

It will be left to the Investigator’s clinical judgment to decide whether or not an AE is of sufficient severity to require the participant’s removal from treatment. A participant may also voluntarily withdraw from treatment due to what he or she perceives as an intolerable AE. If either of these occurs, the participant must undergo an end of trial assessment and be given appropriate care under medical supervision until symptoms cease, or the condition becomes stable.

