## Reporting Procedures for Serious Adverse Events

Safety reporting will be from baseline to the 18 month follow up visit.

Adverse events may also be recorded by the participant using the trial telephone number or email. Participants will be directly asked about adverse events at each study visit.

A serious adverse event (SAE) occurring to a participant should be reported to the REC that gave a favourable opinion of the study where in the opinion of the Chief Investigator the event was ‘related’ (resulted from administration of any of the research procedures) and ‘unexpected’ in relation to those procedures. Reports of related and unexpected SAEs should be submitted within 15 working days of the Chief Investigator becoming aware of the event, using the HRA [report of serious adverse event](http://www.nres.npsa.nhs.uk/docs/forms/Safety_Report_Form_(non-CTIMPs).doc) form (see HRA website).

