## Exercise Training

Exercise training is safe and the established global benefits to health and well-being outweigh negative complications and risks. However, risk of injury, medical complications and serious adverse events are reported in association with exercise participation. Muscle and joint soreness and minor musculoskeletal are common adverse effects of exercise training, however the risk of a serious adverse event including sudden cardiac death or non-fatal cardiac event is reported as below 0.01 per 10000 hours of participation. The following injuries and medical complications may be expected in association with exercise training:

| Accidental Injury | Fall (resulting in admission)  Head injury (resulting in admission)  Road traffic or pedestrian injury |
| --- | --- |
| Allergy | Insect bite  Seasonal allergy exposure |
| Cardiovascular | Exertional Hypotension  Tachycardia  Arrhythmia  Bradycardia  Sudden cardiac event and death |
| Dermatological | Abrasions and Blisters  Dry skin  Fungal infection |
| Gastro-intestinal | Dehydration  Irritable bowel  Increased bowel frequency  Gastro-intestinal blood loss  Gastrosphageal reflux |
| Gynaecology | Irregular menstrual cycle |
| Musculoskeletal | Muscle soreness  Muscle injury  Muscle cramps  Joint injury including sprain  Tendon injury or strain  Ligament tears  Joint inflammation or swelling  Fracture |
| Neurological | Back pain  Nerve entrapment  Headache  Pain |
| Renal | Haematuria  Proteinuria  Exercise associated hyponatraemia |
| Respiratory | Upper respiratory tract infection or viral illness  Exercise induced broncho-spasm |
| Thermal | Heat Cramps  Hyperthermia, Heat exhaustion if exercising in hot/humid environments  Heatstroke  Hypothermia if exercising in cold environments |

Participants shall report adverse events through either hard-copy or secure, computer-based reporting forms. All participants will be briefed to directly seek appropriate clinical care as needed for any adverse events.

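### The Data Monitoring Committee's listed annual review omits adverse events, and the protocol assigns no independent body to compare harm between arms

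*Supplement*

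**What the plan says.** **Oversight (protocol section 13).** On the Data Monitoring Committee (DMC), the protocol says "A data monitoring committee is being formed" and then gives its task: "Rates of recruitment, trial compliance, measurement of primary outcome and study attrition will be review annually by the independent members" of that committee. On the Trial Steering Committee (TSC) it says "A Trial Steering Committee has been formed to oversee the conduct of the trial". The TSC includes the Chief Investigator as well as some independent members. No review of adverse events is listed for either body.

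**Recording (10.1 and 10.2).** Section 10.1 defines an adverse event only for a participant who has been given the exercise intervention. Section 10.2 is broader: "All AEs occurring during the trial / or until completion of the final study visit that are observed by the Investigator or reported by the participant" are to be recorded on the CRF. Relatedness is judged by a medically qualified investigator or the sponsor.

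**Reporting outside the team (10.4).** A serious adverse event goes to the ethics committee where, in the Chief Investigator's opinion, "the event was ‘related’ (resulted from administration of any of the research procedures) and ‘unexpected’ in relation to those procedures".

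**Foreseen harms (10.7).** The protocol accepts that "risk of injury, medical complications and serious adverse events are reported in association with exercise participation". It then tabulates injuries and complications that may be expected with training. These include joint and tendon injury, fracture, arrhythmia, heatstroke, and sudden cardiac event and death.

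**Analysis (11.1 and 11.3).** Neither section describes a comparison of adverse events between arms.

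**The concern.** In an open exercise trial the harms most likely to differ between arms are those that look ordinary one at a time: strains, sprains, falls, palpitations. Judging each case for relatedness and expectedness cannot show that one arm has more of them than the other. Only a table by arm can, and the useful reader of that table is someone independent of delivery who can recommend a change.

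The population adds some weight. Section 8.3 lets people with clinic pressure from 140/90 to 159/99 mmHg and no end-organ damage proceed. Half the sample is to be preterm-born, a group in which the Background section reports reduced right ventricular ejection fractions in a minority. If the section 13 list is followed as written, the independent members receive recruitment, compliance, outcome-measurement and attrition figures, and no harm data.

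**Working it through.** The protocol states no figure on this point, so the check is mainly of the text.

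**Step 1. Is harm on the DMC list?** Section 13 names four items: recruitment, compliance, measurement of the primary outcome, and attrition. None is an adverse event measure.

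**Step 2. Does any other section supply an independent comparison by arm?**

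| Section | What it provides | Independent and by arm? |
|---|---|---|
| 10.2 | CRF recording; relatedness judged by investigator or sponsor | No |
| 10.4 | Single serious events to the ethics committee, if related and unexpected | Independent, but not by arm |
| 11.1, 11.3 | Efficacy and explanatory analyses | No harm analysis described |
| 12.1 | Sponsor and host access for monitoring and audit | No |
| 13 | GCP monitoring; TSC oversight of conduct | No harm review stated |
| 14.5 | Review of an injured participant's safety to continue | Case by case |
| 14.11 | Annual progress report to ethics committee, host and sponsor | No safety content specified |

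**Step 3. What passes through the 10.4 filter?** An event must be serious, related and unexpected. Most items in the 10.7 table, such as soreness, cramps and sprains, would usually not be serious. The grave ones, such as arrhythmia, fracture and sudden cardiac event, are on a list of events that may be expected. The protocol does not say that 10.7 is the reference for expectedness in 10.4. If it is used that way, which is the natural reading, a listed event need not be reported even when it is serious and related.

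**Step 4. Would a comparison be valid as the rules stand?** On 10.1 read literally, an untoward occurrence in a control participant is not an adverse event. On 10.2 all adverse events are recorded. Section 10.4 has participants asked about adverse events at each study visit, which suggests both arms were meant. The passages need to be reconciled, because a table by arm has no comparator if control events are not captured.

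**Step 5. What could such a table show?** This is an illustration only. The event proportions are assumptions, since the documents give none. With n per arm, proportions p1 and p2, and pbar their mean:

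power = Φ{[(p2 − p1) − 1.96·√(2·pbar·(1 − pbar)/n)] / √[(p1(1 − p1) + p2(1 − p2))/n]}

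For p1 = 0.05, p2 = 0.15, n = 100 (200 randomised 1:1): (0.10 − 1.96 × 0.0424)/0.0418 = 0.40, which gives a power of 0.66.

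| Assumed proportions (control, exercise) | n = 33 per arm | n = 100 per arm |
|---|---|---|
| 5%, 15% | 0.27 | 0.66 |
| 5%, 20% | 0.45 | 0.90 |
| 10%, 25% | 0.36 | 0.80 |

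A cumulative table could thus show a clear excess of common events by full enrolment. With about a third of participants it would miss most such excesses. It would say little about rare events.

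**The case against.** **Silence is not proof.** Section 13 does not call its list exclusive, and no DMC charter is shown. Remit and report contents are often set in a charter. The supplementary appendix (section 1) calls the committee a DSMC and says it and the TSC asked for the multiple imputation analysis. This stands as a limit: a reader might infer that no independent body ever compared harm, and the documents do not establish that. They establish that the protocol assigns the task to nobody. An extra letter in an acronym does not assign it.

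**Other people outside delivery see some safety information.** The sponsor may judge relatedness, monitors and auditors have access, and the ethics committee receives annual reports. So it would be wrong to say that harm reaches no one outside the trial team. None of these routes is a stated review by arm.

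**Steering review does not demonstrably stop early.** A reader might take the TSC meeting after about a third of second visits as its last, and count later training hours as unsteered. Section 13 lists upcoming meetings without naming a final one, and the appendix shows later TSC input. Since no TSC harm review is stated at any meeting, such hours would not measure missing harm review in any case.

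**The DMC list has partial signals.** Withdrawal for a contraindication to exercise (8.9) would count towards attrition. Measurement of the primary outcome may mean values or only completeness, so it cannot be claimed that uncontrolled pressure in the control arm would escape the committee.

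**Serious events should be very rare.** Section 10.7 cites a serious event rate below 0.01 per 10,000 hours. Even with 100 exercisers attending all 48 sessions of 90 minutes (100 × 72 = 7,200 hours), that is under 0.01 × 7,200/10,000 = 0.0072 events. Section 7.3 also excludes relevant cardiac disease. This stands for serious cardiac events. It does not cover the injuries and lesser complications that 10.7 calls common or expected, which is where a difference between arms is plausible.

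**Conclusion.** The point holds in this form: the independent members' stated review contains no harm data, the only independent recipient of safety reports sees filtered single cases, and no section assigns a comparison of adverse events by arm. This is more than a missing detail, because the stated list, followed exactly, leaves an excess of individually expected events unseen by those asked to watch the trial. It should be corrected. It does not bear on the validity of the blood pressure analysis.

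The size cannot be given in events, because the documents report no rates by arm. The conclusion rests on two assumptions: that no charter outside these documents already gives the DMC this remit, and that the 10.7 table informs what counts as unexpected in 10.4. If the second fails, more serious events reach the ethics committee, but still one at a time and not by arm.

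**What to change.** 1. In section 13, add to the DMC's annual review all adverse and serious adverse events by arm, as numbers of participants and of events, by the 10.7 categories. Include events from study procedures (exercise testing, blood sampling, imaging) and withdrawals for adverse events. If a charter already provides this, a cross-reference is enough.
2. State in section 13 that the DMC may make recommendations to the TSC.
3. Reconcile the definition in 10.1 with the recording rule in 10.2, so that control-arm events are captured and the comparison is valid.

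The cost is wording in sections 10 and 13 and one extra table a year, from data that 10.2 already places on the CRF, for a review that is already planned. No new visits or procedures are needed. Because exercisers are monitored weekly (section 9) and controls are not, the table should mark events elicited at study visits, so that an excess caused by closer contact is not mistaken for harm.
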